### Randomization and blinding

For each group, a block randomization list is provided, which is generated prior to initiation of the study using a random seed number via SAS PROC PLAN software (SAS Inc., Cary, NC, USA). Randomization occurs after screening and baseline assessments, and patients will be randomized in a 1:1:1 fashion to receive one of three treatments. Participants will be randomized using web-based randomization service, which is an online, central randomization service provided by Longhua Clinical Trials Support Unit in Shanghai, China. This service will not release the randomization sequence until the interventions are assigned.

All investigators involved will be blinded to group assignment. An independent data analyst and the research nurse who assigns subjects will not be blinded to treatment status and will not take part in any other part of this trial.

If, after the first administration, any clinically significant adverse event is potentially related to JWYH treatment, the study physician will re-evaluate the participant and local PI or delegate will decide whether a non-blinded procedure is necessary. If non-blinding is considered required, the actual allocation information will be provided to the physician.

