### Participants

Patients who meet the inclusion criteria and are not excluded by the exclusion criteria (Table 1) will be invited to participate in this study. Every year, the collaborating centers have many asthmatic outpatients and inpatients, which significantly facilitates subject recruitment. Prior to the start of the study, patients are informed of all aspects of the study. The PIs and/or research nurse explain the study in detail, answer questions, ensure that informed consent will be given by each patient, and that appropriate signatures are obtained prior to the start of the study.

**Table 1 Tab1:** Inclusion and exclusion criteria

Inclusion criteria	
1. Patient diagnosed with chronic persistent asthma	
2. Annual uncontrollable time ≥ 3 months	
3. Patients who have given written informed consent	
Exclusion criteria	
1. History of upper upper/lower respiratory infection in the previous 1 month	
2. History of long-term controller medication use for asthma (orally or intravenously administered corticosteroid therapy) within the preceding 1 month	
3. History of antibiotic use in the previous 1 month	
4. History of life-threatening asthma	
5. History of chronic lung diseases	
6. History of serious disease of the heart and cerebrovascular disease	
7. History of severe liver or renal dysfunction or disease	
8. History of severe disease in the hematopoietic system	
9. History of immunodeficiency (including, but not limited to, HIV-positive detection)	
10. History of any other condition (such as known drug or alcohol abuse or psychiatric disorder)	
11. Are currently enrolled in, or discontinued within the last 30 days from, a clinical trial involving an investigational product or non-approved use of a drug or device	
12. History of allergies to the component of the investigational drugs	
13. Smoking within the past year	
14. Contraindication to induced sputum collection method on history or examination	
15. Any serious medical condition which, in the opinion of the investigator, would pose a significant risk to the patient or interfere with the interpretation of safety, efficacy, or pharmacodynamic data	

After the informed consent form (ICF) is signed and dated, a patient is considered “eligible” to enter the trial, is assigned a patient number, and is randomized to one of three treatment arms.

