Where appropriate, subgroup analyses, will be provided for effectiveness and safety endpoints, and will be based on baseline disease characteristics.

Data are analyzed using SAS 9.4 software (SAS Institute Inc., Cary, NC, USA). Unless otherwise noted, all treatment effects are employed at a two-sided α level of 0.05 and confidence intervals (CIs) will be calculated at 95%, two-sided.

For exploratory analysis of the airway microbiome, alpha diversity will be estimated as the number of observed OTUs and by the Chao1 Index, Simpson Index, Shannon Index, and phylogenetic alpha diversity (PD). UniFrac beta-diversity metrics will be compared between treatment groups using the PERMANOVA test from R’s vegan library [33]. In addition, UniFrac measures the phylogenetic distance between two samples as the fraction of the branch length of the phylogenetic tree, and are widely used to determine whether communities are significantly different [34]. Community dissimilarities will be estimated using principal coordinates analysis (PCoA). OTU abundance differences will be analyzed by assuming rarefied (Fisher’s exact test, respectively) and non-rarefied (metagenomeSeq zero-inflated Gaussian [35]) data. Statistical significance is determined by permutation tests using 10,000 permutations. In addition, core microbiome analyses will be performed to identify resident bacteria, after applying Benjamini-Hochberg FDR adjustments for multiple comparisons.

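### The data analyst is unblinded by design, without a stated reason, although the primary model and per-protocol membership still depend on choices made from the data

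*Protocol article*

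**What the plan says.** Randomization and blinding states: "All investigators involved will be blinded to group assignment". It then makes two exceptions: "An independent data analyst and the research nurse who assigns subjects will not be blinded to treatment status". The same sentence adds that these two "will not take part in any other part of this trial". Allocation is central: "Participants will be randomized using web-based randomization service".

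Statistical methods fixes most of the primary analysis: the week-4 change in ACT, ANCOVA with baseline ACT, the mITT set, LOCF and a two-sided 5% level. Sample size adds the testing order, high dose against placebo first and low dose only if that succeeds. The center term is not fixed. A treatment-by-center interaction is looked for, and center enters as a random effect only if one is found. No significance level or other criterion is given for that look.

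The per-protocol set repeats the efficacy analysis in patients without major violations. The section Major protocol deviation describes these partly by their effect on risk, rights or study integrity, and partly by a list that includes omitted procedures and dispensing errors.

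Data management says that the database is locked and then analyzed with the PI's agreement and review. It mentions no step at which the treatment key is released.

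**The concern.** The natural reading is that the data analyst analyzes the data. Being barred from every other task does not help there, because analysis is the task in question. On that reading, the person who decides whether an interaction exists, and who may help decide which deviations are major, knows throughout which patients had high dose, low dose or placebo.

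The center decision sits in the primary model. It changes the standard error for high dose against placebo, and that comparison is the gate for the low-dose test. Knowledge of the arms at that moment exposes the confirmatory result to a charge of bias that could easily be avoided. The stated logistics do not obviously call for it: allocation comes from a web service, and Treatments administered says that the products look alike.

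**Working it through.** **1. The plan's own figure.** Inputs from Sample size: difference 2, SD 4, two-sided 5%, power 80%. n = 2 × 4² × (1.960 + 0.842)² / 2² = 62.8, so 63 per group. The exact t-test calculation gives 63.8, so 64. Allowing for 20% dropout, 64 / 0.80 = 80, and 3 × 80 = 240. The plan's figures reproduce, and nothing below changes them.

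**2. Which choices are open when the analyst already knows the arms.**

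| Element | Status in the article |
|---|---|
| Primary endpoint, ANCOVA, baseline covariate | Fixed |
| mITT set and LOCF | Fixed |
| Two-sided 5%, high dose then low dose | Fixed |
| Center in the primary model | Depends on an interaction look, no criterion |
| Per-protocol membership | Needs judgment on major deviations |
| Exacerbation-rate test, Holm-Bonferroni, subgroups | Left to later judgment; a SAP may settle them |

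For the primary analysis, one item is open: the center term. Its effect cannot be computed, because the article gives neither the between-center variance nor the number of patients per center.

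**3. What coding the arms would achieve.** Three arms can be matched to A, B and C in 3 × 2 × 1 = 6 ways, and there are three pairwise contrasts. Without the key, the analyst knows neither the favored direction nor which contrast is the primary one. That is real protection when center and the per-protocol set are decided.

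**4. What coding would not achieve.** Take the exacerbation rate, where a t test or a Wilcoxon test may be used. A null simulation (64 per arm, 40,000 runs, simulation error about 0.1 percentage point) took the smaller of the two p values. The distributions are assumptions.

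| Assumed distribution | t alone | Wilcoxon alone | Smaller p |
|---|---|---|---|
| Normal | 5.2% | 5.2% | 6.2% |
| Poisson, mean 0.3 | 4.9% | 4.9% | 6.0% |
| Negative binomial, mean 0.5 | 4.8% | 5.0% | 6.9% |

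This inflation needs only sight of the p values, not knowledge of the arms. Coding does not remove it; a test fixed in advance does.

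**5. The assigning nurse.** The article gives "a block randomization list is provided, which is generated prior to initiation of the study using a random seed number" and a 1:1:1 ratio, but no block size. With k patients per arm in a block of 3k, someone who has seen every earlier allocation in the block is certain of the next arm for a fraction 1/(2k + 1) of patients.

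| Assumed block | Next arm certain | Best guess correct (chance 33%) |
|---|---|---|
| 3 | 33% | 61% |
| 6 | 20% | 56% |
| 9 | 14% | 53% |
| 12 | 11% | 51% |

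These figures apply only if one person knows the block size, sees the whole block and also influences who is enrolled. The article states none of these.

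**The case against.** **The analyst's role is not stated.** The person is called independent, and may only hold the list or support randomization. If so, the concern largely falls away. This stands as a condition, and it is why the fix begins by asking for the role. It does not remove the point: no other analyst is named, and the ordinary meaning of the title is the one taken here.

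**A SAP may close the open choices.** This is fair. An interaction threshold, the exacerbation-rate test and the rule behind "Where appropriate, subgroup analyses, will be provided for effectiveness and safety endpoints" are commonly left to a SAP, so their openness is not a finding in itself. What remains is a rule that the article does state, namely that the analyst is unblinded.

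**Coded arms do not prevent selective analysis.** This is correct, as step 4 shows. The gain is limited to removing knowledge of the active arm.

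**A stronger reading about the nurse.** A reader might infer that the unblinded nurse also takes consent, because Participants says "The PIs and/or research nurse explain the study in detail, answer questions", and that concealment is therefore compromised. The document does not support this. The sentence that unblinds the assigning nurse also bars that nurse from all other trial work, and the two sections share only a job title. With eight centers, and two study nurses mentioned for data entry alone, several nurses are evidently involved. The service withholds the sequence until assignment. If one central list serves all sites, a nurse who sees one site's allocations cannot reconstruct a block. It also cannot be said that the nurse has no need to be unblinded: numbered kits are not described, and Treatments administered gives different granule weights by arm.

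**Conclusion.** The point holds for the analyst. The article unblinds the data analyst, gives no reason, and makes one element of the primary model depend on a look at the data; per-protocol membership adds a second matter of judgment. This assumes that the analyst named runs the efficacy analysis. The size of any bias cannot be derived from the document, and no figure in the plan changes. The weakness is moderate: most of the primary analysis is fixed, and the per-protocol set serves only to check robustness.

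For the nurse, the conclusion is limited to a shared job title that should be clarified. The predictability figures in step 5 illustrate what would follow under conditions that the article does not state; they are not evidence of a breach.

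**What to change.** 1. In Randomization and blinding, state what the unblinded analyst does. If that person only holds the allocation list, say so and name a separate blinded analyst for efficacy.
2. Otherwise, have whoever runs the efficacy analysis work with arms coded A/B/C. Release the key only after the database is locked and the analysis populations and models, including the center decision, are signed off. Keep variables that reveal the arm, such as granule weight, out of the coded data set.
3. Do not present coding as a guard against selection on p values. Signing off the models before the key is released does not close that gap unless the choices were fixed in advance.
4. Add one sentence saying that the nurse who assigns patients is not the research nurse who takes consent under Participants.

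The cost is small: a separate holder for the code, a short unblinding step after lock, and a few lines of text. Sample size, visits and data collection do not change.

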### Data collection and management

After screening and completing a set of questionnaires and evaluations, participants will attend two assessment visits and three follow-up visits (Fig. 2). Demographic information (date of birth, gender, etc.) and medical condition (medical history, concomitant medication, etc.) are recorded.

**Fig. 2 Fig2:**
[figure not shown]
Schedule for enrollment, intervention, and assessment. *List specific time points in this row. [1] Vital signs: height, weight, body temperature, blood pressure, and heart rate. [2] Lung function tests: *FEV*_*1*_ forced expiratory volume in 1 s, *FEV*_*1*_*/FVC*, *FVC* forced vital capacity, *IC* inspiratory capacity, *TLC* total lung capacity. [3] Laboratory tests: blood, urine, feces, electrocardiogram, kidney and liver function

### Lung function

Lung function will be assessed by FEV_1_, FVC, and PEF. Lung function tests are conducted at baseline and every 4 weeks with standardized equipment (Erich Jaeger UK Ltd., Market Harborough, UK Jaeger Master-Screen, Germany) and standardized procedures recommended by the American Thoracic Society (ATS) [28]. After randomization, a peak flow meter and asthma diary will be given to each patient, who will be trained to use the equipment to record their PEF daily. FeNO will be conducted according to ATS standards [29].

### Collection of sputum

At the time of randomization, samples of induced sputum will be collected from subjects, as well as at 2 weeks, 4 weeks, and 8 weeks after enrollment. From each subject, sputum will be induced by inhalation of a nebulized solution of 3% saline. To minimize oral contamination, patients rinse their mouth and clean their nasal passages before sputum induction. Sputum samples are collected into sterile cups, and the entire procedure lasts about 15 min. Sputum plugs are selected and differential cell counting is performed. An equal weight of dithiothreitol is added to the sputum plug to dissolve mucus. All samples will be stored at − 80 °C prior to bacterial deoxyribonucleic acid (DNA) extraction.

### Data management

All records will be collected in Case Report Form (CRF) files, and data input will be employed using a double independent entry to ensure data accuracy. Once verification is completed, data will be securely stored.

Original study forms will be entered and kept on file at the participating site. All forms are sent to the coordinating center, and data are entered into EpiData 3.1 software by two study nurses (independent double-data entry by two individuals). Data errors and inconsistencies will be checked during the entry process. Files are stored in a secure and accessible place and manner. Security measures will be regulated by a user identification code and password. Monthly backups are stored on CD media. Finally, the database will be locked and analyzed under the agreement and confirmed review of the PI.

The PI will be given access to the cleaned data sets. Site investigators will have direct access to the data sets from their own sites, and will have access to the data on other sites on request.

### Safety

In China, *Yang He* decoction has been used for hundreds of years, and the dosage of JWYH used in this study is within the recommended range based on the *People’s Republic of China Pharmacopeia* (2015 edition). Due to the long-time clinical use and preliminary studies of JWYH from January 2017 to April 2017, no adverse effects were observed during the treatment and follow-up period. Moreover, we will employ a series of measures, including subjective description and laboratory tests, that especially focus on gastrointestinal intolerance, heart, liver, and kidney damage to assess the safety of JWYH from the time of enrollment through the follow-up period. During each visit, patients will be asked about any adverse effects during the study period. In addition, laboratory tests will be conducted on blood, urine, feces, electrocardiogram, kidneys and liver function prior to and after treatment. If adverse events are observed, we are prepared to immediately provide appropriate examination and treatment.

Any adverse event that occurs to a subject will be recorded in the CRF regardless of relationship to the study intervention. In case of any serious adverse events (SAEs), the intervention will be immediately stopped and a detailed description of the time, severity, relationship with the drug and the measures taken of the SAE based on standard operation procedures (SOPs) of the China Food and Drug Administration (CFDA) will be given. In addition, SAEs will be reported to the PI, Steering Committee, Ethics Committee, and the sponsor within 24 h.

### Sample size

Sample size calculations are based on the primary endpoint (ACT score at 4 weeks). At the 5% significance level, a total of 64 patients per group is required to achieve 80% power and to determine an increase of 2 points in the ACT score between the high-dose TCM plus usual care group and the placebo plus usual care group, assuming that the standard deviation of the groups is equal to 4 [30]. If the previous hypothesis is rejected, then the difference of 1.5 points in ACT score between the low-dose TCM plus usual care group and the placebo plus usual care group at the 5% significance level is tested. With an estimated dropout rate of 20%, a total of 240 patients is enrolled. If the initial hypothesis is not rejected, subsequent comparison is considered exploratory, and no conclusion is made [31, 32].

### Statistical methods

The modified intent-to-treat (mITT) population is defined as randomized patients who receive at least one dose of randomized treatment with at least one post-randomization ACT value, classified according to their assigned treatment. The mITT analysis set is used for efficacy and exploratory analyses. Last observation carried forward (LOCF) imputation is used for missing data in the mITT population. A per-protocol (PP) population is defined as randomized patients without major protocol violations. The PP analysis set is used to repeat the efficacy analysis and to assess the robustness of the results. The safety population is defined as all patients who receive at least one dose of randomized treatment and for whom any post-dose data are available, classified according to the treatment received. The safety population will be used for the analyses of all safety measures.

For the primary outcome, changes in ACT scores from baseline to week 4 will be analyzed by means of analysis of covariance (ANCOVA). Treatment and center interactions will be examined, and, when an interaction does not exist, the ANCOVA model includes treatment and baseline ACT total score as explanatory variables. Otherwise, ANCOVA analysis will include the baseline ACT total score as covariate, treatment as a fixed effect, and the center as a random effect. Secondary outcomes (ACT at 8 weeks, FEV_1_, and FVC) are assessed in a similar fashion. AER will be analyzed using a *t* test or Wilcoxon rank-sum test as appropriate, and the Holm-Bonferroni method is used to control type I errors if necessary.

A mixed-model repeated measures (MMRM) analysis will be used to assess PEF changes. Comparisons will be based upon the contrast between treatments at week 4 (day 28) and week 8 (day 56). Model-based point estimates, 95% confidence intervals, and *p* values will be calculated. A *p* value < 0.05 is considered statistically significant.

For exploratory analysis, MMRM analysis uses all available ACT total score through the week 16 (day 112) visit, and comparisons will be based upon the contrast between treatments at week 16 (day 112). Model-based point estimates, 95% CIs, and *p* values are calculated.

Any adverse event will be recorded in the CRF regardless of relationship to the study intervention. Safety endpoints will be analyzed using summary statistics (frequency, count, percentage).

Where appropriate, subgroup analyses, will be provided for effectiveness and safety endpoints, and will be based on baseline disease characteristics.

Data are analyzed using SAS 9.4 software (SAS Institute Inc., Cary, NC, USA). Unless otherwise noted, all treatment effects are employed at a two-sided α level of 0.05 and confidence intervals (CIs) will be calculated at 95%, two-sided.

For exploratory analysis of the airway microbiome, alpha diversity will be estimated as the number of observed OTUs and by the Chao1 Index, Simpson Index, Shannon Index, and phylogenetic alpha diversity (PD). UniFrac beta-diversity metrics will be compared between treatment groups using the PERMANOVA test from R’s vegan library [33]. In addition, UniFrac measures the phylogenetic distance between two samples as the fraction of the branch length of the phylogenetic tree, and are widely used to determine whether communities are significantly different [34]. Community dissimilarities will be estimated using principal coordinates analysis (PCoA). OTU abundance differences will be analyzed by assuming rarefied (Fisher’s exact test, respectively) and non-rarefied (metagenomeSeq zero-inflated Gaussian [35]) data. Statistical significance is determined by permutation tests using 10,000 permutations. In addition, core microbiome analyses will be performed to identify resident bacteria, after applying Benjamini-Hochberg FDR adjustments for multiple comparisons.

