### Treatments administered

Patients are randomly assigned to groups to either receive a high-dose JWYH by oral administration, a low-dose JWYH by oral administration, or a placebo twice daily for 4 weeks (28 days). After baseline assessment, all participants will maintain or receive background therapy with ICS or a β_2_-adrenoceptor agonist as usual care.

Participants in the high-JWYH-formula group receive 18.5 g JWYH granules twice daily for 4 weeks, whereas participants in the low-JWYH-formula group receive 9.25 g of JWYH granules twice daily for 4 weeks. Patients in the placebo group are given placebo granules (9.25 g twice daily for 4 weeks). Drugs are identical in appearance, shape, size, and packaging.

Whole ingredients of the intervention formula include *Rehmanniae Radix Praeparata* (*Shu Di Huang*) 15 g, *Cinnamomi Cortex* (*Rou Gui*) 3 g, *Ephedrae Herba* (*Ma Huang*) 4.5 g, *Cervi Cornus Colla* (*Lu Jiao Jiao*) 3 g, *Sinapis Semen* (*Bai Jie Zi*) 6 g, *Zingiberis Rhizoma Preparatum* (*Pao Jiang*) 6 g, *Clycyrrhizae Radix Et Rhizoma* (*Gan Cao*) 6 g, *Asari Radix Rhizoma* (*Xi Xin*) 3 g, and *Codonopsis Radix* (*Dang Shen*) 9 g. All herbal granules are produced by the Sichuan Green Pharmaceutical Technology Development Limited by Share Ltd. in Sichuan, China. The dosage for all three groups includes one pack of granules that needs to be soaked in 100 mL of boiling water, taken orally twice daily, after breakfast and supper.

At each study visit, adherence to intervention is monitored and participants are asked to return all study containers with any unused packs of granules, including all empty containers. Once the patient is randomized, study sites will take every reasonable effort to follow the patient for the entire course of the study. All examination and transportation costs are covered and the results of symptoms and physical examinations will be explained at every visit. Prior to every visit, messages will be sent through WeChat or by phone to remind patients of the upcoming data collection.

Patients who discontinue the assigned treatment based on serious adverse events (SAEs), or poor compliance (more than 14 days without taking medicine), or in cases when the attending physician requests that the patient should undergo orally or intravenously administered corticosteroid therapy because symptoms worsen after screening.

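### LOCF is the only missing-data rule for the efficacy analyses; it can move the treatment difference either way at week 8, and at week 4 if ACT is also scored earlier

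*Protocol article*

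**What the plan says.** All references are to the protocol article.

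- **Statistical methods, missing data.** "Last observation carried forward (LOCF) imputation is used for missing data in the mITT population". That population is randomized patients with "at least one dose of randomized treatment with at least one post-randomization ACT value", and "The mITT analysis set is used for efficacy and exploratory analyses".
- **Statistical methods, models.** The primary analysis is an ANCOVA of ACT change to week 4. Week-8 ACT, FEV1 and FVC follow the same approach. The only robustness check named is a per-protocol repeat.
- **Statistical methods, exploratory.** For the same score, "MMRM analysis uses all available ACT total score through the week 16 (day 112) visit", with the contrast at week 16. PEF also has an MMRM, with contrasts at weeks 4 and 8.
- **Sample size.** "With an estimated dropout rate of 20%, a total of 240 patients is enrolled". The 20% is not divided by arm or visit.
- **Treatments administered.** Reasons for stopping assigned treatment are serious adverse events, poor compliance, and a physician's request for "orally or intravenously administered corticosteroid therapy because symptoms worsen after screening". The same section asks sites to keep following every randomized patient.
- **Timing of ACT.** The outcome sections name ACT at weeks 4, 8 and 16. A 2-week time point is given for sputum only. The schedule figure (Fig. 2) is not shown.

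**The concern.** LOCF assumes that a patient's score would have stayed exactly where it was last seen, and then analyzes that guess as data. The protocol itself gives reasons to doubt this. Some patients stop because they worsen, so a score carried past that point may come from before the deterioration. Treatment also ends at week 4, so a week-4 score carried to week 8 puts an end-of-treatment value into an off-treatment visit.

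If the arms lose patients at different rates, the error does not cancel. The per-protocol repeat changes who is analyzed, not what is assumed about missing scores, so it would not reveal the problem. At stake are the size of the estimated effect, the 5% error rate, and the testing of the low dose, which depends on the high-dose result.

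**Working it through.** **1. The plan's own figures.** Inputs from Sample size: difference 2, SD 4, two-sided 5%, power 80%. The normal approximation is n = 2 × (1.96 + 0.84)² × 4² / 2² = 62.7, so 63 per group. The noncentral t gives 79.5% power at 63 and 80.1% at 64, so 64 is right. Then 64 / 0.80 = 80 per arm and 3 × 80 = 240. The stated figures reproduce. A 20% loss is 16 of 80 per arm, or 48 of 240.

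**2. Where LOCF can act.**

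| ACT schedule | Week-4 primary | Week 8 |
|---|---|---|
| ACT also scored before week 4 | An earlier score is carried to week 4 | An earlier score is carried to week 8 |
| Week 4 is the first post-randomization ACT | No post-randomization score to carry; patients never scored are outside mITT; patients first scored later are inside it with no stated handling | The week-4 score is carried to week 8 |

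Lung function is measured at baseline and every 4 weeks, so LOCF carries week-4 FEV1 and FVC to week 8.

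**3. Size if leavers would have worsened.** Suppose leavers in both arms would have fallen g points after their last score. The shift in the active-minus-placebo difference is g × (active dropout − placebo dropout). The values of g and the splits are assumptions.

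| Dropout, active/placebo | g = 1 | g = 2 | g = 4 |
|---|---|---|---|
| 20%/20% | 0 | 0 | 0 |
| 10%/30% | −0.2 | −0.4 | −0.8 |
| 30%/10% | +0.2 | +0.4 | +0.8 |

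Against the planned 2 points, 0.2 to 0.8 is 10% to 40% of the effect.

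**4. Simulation with dropout driven by observed scores.** There were 2,000 trials per scenario with 80 per arm. Assumptions: baseline and two later visits, SD 4, correlation 0.6, placebo mean gain 1 then 2, treatment difference 1 then 2, and dropout after the first later visit more likely with a low score. The comparator is a likelihood estimate equivalent to MMRM under this dropout pattern.

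| True difference | Realized dropout, active/placebo | LOCF estimate | MMRM-type estimate | LOCF rejections | MMRM-type rejections |
|---|---|---|---|---|---|
| 2 | 24%/24% | 1.77 | 2.01 | 88.6% | 92.9% |
| 2 | 13%/33% | 2.22 | 2.03 | 97.5% | 93.6% |
| 2 | 33%/13% | 1.34 | 2.01 | 69.4% | 93.8% |
| 0 | 24%/24% | 0.00 | 0.01 | 5.6% | 5.2% |
| 0 | 13%/33% | 0.34 | 0.01 | 9.2% | 4.8% |
| 0 | 33%/13% | −0.33 | 0.00 | 9.2% | 5.1% |

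Two further simulations under similar assumptions gave 1.45 and 1.46 at the low end, 2.28 and 2.27 at the high end, and type I error of 9% to 10%. At equal dropout the LOCF error rate is close to nominal, so the damage here comes from bias rather than from intervals that are too narrow.

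**5. Check by hand.** In this simulation leavers would on average have risen after their last score. The null rows imply an effective rise of 0.33 / 0.20 = 1.65 points. In the active arm it is 1 more, because the treatment difference grows by 1. The expected shift is placebo dropout × 1.65 − active dropout × 2.65:
- 24%/24%: 0.40 − 0.64 = −0.24
- 13%/33%: 0.54 − 0.34 = +0.20
- 33%/13%: 0.21 − 0.87 = −0.66

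Added to about 2.0, these give the tabled 1.77, 2.22 and 1.34. The sign is opposite to step 3 because leavers here rise rather than fall. The direction therefore depends both on which arm loses more and on how leavers would have fared.

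**6. Unseen worsening.** Take 25% active and 15% placebo dropout, no effect in stayers, and leavers 5 points worse at the target visit. The true difference is −5 × (0.25 − 0.15) = −0.5. With a 1-point deficit already visible in leavers, LOCF gives −0.10 and the MMRM-type estimate −0.06 to −0.09 (correlation 0.4 to 0.8). Another run of this kind gave −0.19 and −0.03 for a true −0.48.

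**The case against.** **Reach into the primary endpoint.** A reader might infer that LOCF distorts the week-4 analysis as a matter of course. The document does not establish that, because no shown text places an ACT before week 4. If week 4 is the first post-randomization score, LOCF carries nothing to it. This stands, and the point is worded accordingly.

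**Stopping treatment is not the same as a missing score.** The corticosteroid clause concerns assigned treatment, and sites are asked to keep following patients. Someone who stops for worsening may still have an observed ACT. This also stands: carrying a pre-deterioration score is a likely case, not the general one.

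**MMRM as the cure for hidden harm.** In step 6 LOCF shows −0.10 for a true −0.5, and a reader might infer that LOCF hides 80% of the harm and that MMRM would reveal it. It would not. MMRM assumes data missing at random and recovers slightly less than LOCF there. The scenario supports a sensitivity analysis, not MMRM over LOCF.

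**Invented splits.** The document gives only an overall 20%. The sizes are illustrations, and at equal dropout LOCF understates benefit without inflating type I error.

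**A matter for the SAP, or of preference.** Covariance structure and model terms can indeed wait for the SAP, and their absence for the ACT MMRM is no fault. Using different models for primary and exploratory endpoints is not in itself a contradiction. But LOCF is a rule this document fixes, so it can be judged here.

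**Conclusion.** The concern holds in this limited form. LOCF is the sole stated rule for the mITT efficacy analyses, and it can bias the treatment difference in either direction when dropout differs by arm. The results in step 4 assume splits of roughly 10% against 30%, SD 4, correlation 0.6, and dropout related to observed scores; step 3 gives shifts of 0.2 to 0.8 points under a simple decline.

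The simulation is indexed by visit order, so it can be read as week 2 to week 4 or as week 4 to week 8. For the second reading, a treatment difference that grows after treatment ends is less natural; the no-effect rows do not depend on that assumption.

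Week-8 ACT, FEV1 and FVC are affected whatever the schedule. The week-4 primary is affected if ACT is scored earlier. If it is not, the mITT definition admits patients first scored after week 4 without saying how they enter the primary analysis.

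One wording conflict also needs resolving. The mITT set, with its LOCF rule, covers the exploratory analyses, yet the week-16 MMRM is to use available scores. The text does not say that filled-in values stay out of it.

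**What to change.** 1. Replace LOCF as the main method with an MMRM on all available ACT scores, including those collected after treatment stops. Use the week-4 contrast as primary and the week-8 contrast as secondary. The exploratory week-16 contrast can come from the same model. State the model terms and covariance structure in the analysis plan.
2. Handle FEV1 and FVC in the same way, so that removing LOCF does not leave them without a rule.
3. State that no LOCF values enter any MMRM, including those for PEF and week-16 ACT. Keep LOCF at most as a sensitivity analysis.
4. Add one delta-adjusted or placebo-based multiple-imputation sensitivity analysis, because MMRM does not recover unseen worsening.
5. State in the text the visits at which ACT is scored, and how patients first scored after week 4 enter the week-4 analysis.

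The cost is wording and minor programming. No new data are needed and the sample size of 240 is unchanged. No interim analysis is planned, so the change can be made before unblinding.
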